**Effectiveness in the optimisation of clinical practice for the primary prevention of T2D (experimental comparison)**	
**Measures**	**Timing and Source**
**Coverage**: Screening indicators (depending on the screening strategy selected by the centre)	
*Case 1* *: T2D screening as part of opportunistic screening for cardiovascular risk in individuals aged ≥45 years or ≥30 years with at least one known risk factor:* • % of non-diabetic patients aged ≥30 years with a cardiovascular risk factor (e.g., hypertension or BMI ≥30 kg/m2 or hyperglycaemia) attending to family doctor office in whom clinical practice guidelines are followed in terms of T2D screening using fasting glucose levels in the previous year; • % of non-diabetic patients aged ≥45 years with no cardiovascular risk factor attending to family doctor office in whom clinical practice guidelines are followed in terms of T2D screening using fasting glucose levels in the previous 4 years.	
*Case 2* *: T2D screening based on a BMI≥25 kg/m2 in individuals aged 40 to 70 years:* • % of non-diabetic patients aged between 40 and 70 years attending to family doctor’s office whose BMI has been measured in the previous year, 12 months after the introduction of the T2D prevention programme in the centres;	Baseline and 12 months after the setting up of the programme
• % of non-diabetic patients aged between 40 and 70 years attending to family doctor’s office with a BMI≥25 kg/m2 who have been screened for T2D using fasting glucose in the previous year, 12 months after the introduction of the T2D prevention programme in the centres.	Electronical Health Record
**Implementation**: Execution of the elements of the intervention programme in high risk patients defined by the presence of prediabetes (fasting glucose 110-125 mg/dl)	
•% of patients whose physical activity levels and diet have been assessed, after the identification of T2D risk; •% of patients who have been given preventative advice concerning the need to increase physical activity and eat a healthy diet, after the identification of T2D risk;	
•% of patients who have been prescribed a plan for increasing physical activity and eating a healthy diet, after the identification of T2D risk;	Baseline and 12 months after the setting up of the programme
•% of high risk patients (fasting glucose 110-125 mg/dl) who have undergone annual testing of fasting glucose and HbA1c.	Electronical Health Record

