In order to analyse the potential associated or modifying characteristics of the effect that the implementation strategy and, within it, the procedures for creating the community of practice could have on clinical practice in the primary prevention of T2D and on clinical outcomes, we studied various different factors at centre, health professional and patient levels:Health centre-based factors: Organisational willingness to change measured with the *Organizational Readiness for Knowledge Translation* (OR4KT) questionnaire [44], the Spanish version of the OR4KT instrument comprising 59 items assessing 6 dimensions and 23 sub-dimensions related to organisational predisposition to knowledge translation: organisational climate, organisational support, contextual factors, change content, leadership, and motivation; leadership assessed with the *Implementation Leadership Scale* (ILS) questionnaire [45]; and various characteristics of the primary care centres, namely, number of registered patients, number of healthcare professionals, mean number of registered patients per family doctor, and a socioeconomic deprivation index for the catchment area that combines variables related to employment (unemployment rate, manual and short-term employment) and education (educational attainment rate among young people and overall).Healthcare professional-related factors: sociodemographic variables (age, sex, professional group, etc.); and professionals’ healthy lifestyle behaviours; and Attitudes, knowledge and skills in the promotion of healthy habits in the clinical context, measured through the *Preventative Activity Questionnaire* [46].Patient-level factors: sociodemographic variables (age, sex, socioeconomic level- deprivation index, etc.); active health problems-morbidity (Adjusted Clinical Groups-ACG, etc.); and frequency of attendance.

Health professionals will be surveyed to obtain information related to the variables at health centre and professional level before the execution of the strategy, immediately after it and 12 months after the introduction of the programmes in the centres.4.Fidelity of the implementation strategy

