#### Sample size

As a worst case scenario regarding the main outcome variables for the optimisation of practices for the prevention of T2D, we hypothesise that we will obtain a rate 30% higher than a baseline level of 50% (that is, 65% in the sequential group vs 50% in the global group) in several of the outcome variables. Considering the participation of 9 centres, an alpha level of 0.05, and an intra-class correlation coefficient (ICC) at centre level of 0.03, we will need a minimum of 425 patients at high risk of developing T2D to be exposed to the prescription of a personalised plan for lifestyle change per group (850 in total) to achieve a statistical power of 80%, allowing for a possible loss of 20% of patients, in the comparison of the aforementioned process indicators related to exposure and execution of the intervention. This scenario is reasonably plausible assuming that 50% of the doctors lists in the centres agree to collaborate with this research and if we consider that, according to data from OSABIDE, an average attendance per year of 875 patients over 45 years of age with prediabetes (baseline glucose ≥110 mg/dl) per group (175 per centre). For exploring a possible modification of clinical outcomes from the prescription of lifestyle changes, namely, a 5% loss of body weight, attributable to the creation of the community of practice, we need 616 patients (308 per group) to achieve a power of 80% to reject the null hypothesis H_0_:p1 = p2 using a bilateral chi-squared test for two independent samples with a level of significance of 5%, considering that 10% of patients will attain such change in one of the groups and 35% in the other, assuming an ICC of 0.03 and a possible loss of 10% of patients at 12 months.

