#### Analysis

All the analyses will be carried out on an intention-to-treat basis and then exploratory analysis will be performed by protocol and subgroup. We will estimate the absolute and relative pre-post intra-centre and between groups differences and the 95% confidence intervals using multi-level logistic regression for dichotomous variables (e.g. proportion of patients with a prescription for lifestyle change). As the sample size for evaluating the implementation objectives is over 20,000 patients, all the comparisons will be significant from a statistical point of view, and hence, emphasis will be placed on the magnitude of these differences, following the Cohen categories based on standardised differences: < 0.5; ≥ 0.5 to ≤ 0.8 and > 0.8 being considered to indicate small, moderate and large effects respectively. Comparisons will be adjusted for potential confounding factors, through stratified analysis and the inclusion of such factors in the regression models following forward and backward strategies guided by the stratified analyses.

To assess the maintenance of implementation outcomes through the 24-month follow-up, mixed-effect generalised longitudinal models will be built with fixed effects (intervention group, effect of time on monthly process indicators and interaction time-intervention) and random effects on the intercept and the slope (for each subject, doctor-centre). Said models will be adjusted for the potential confounding variables, following a forward strategy guided by the stratified analyses. Through these statistical models, we will take into account the intra-class correlation (between doctor-centre) and the hierarchical nature of data: patients nested by medical consultations and these grouped by health centre. All the analyses were carried out using SAS statistical software.

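### Covariates for the randomised nine-centre comparison are chosen stepwise from the data, which could raise type I error to about 10–20% if several centre-level factors are eligible; the set should be fixed in advance.

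*Protocol article*

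**What the plan says.** The Analysis section of the protocol article plans multilevel logistic regression for the main binary indicators, estimating pre-post differences within centres and differences between groups with 95% confidence intervals. These comparisons are then adjusted for possible confounders by stratification and by "inclusion of such factors in the regression models following forward and backward strategies guided by the stratified analyses". The mixed models for the 24-month maintenance outcomes are adjusted "following a forward strategy guided by the stratified analyses". The article gives no candidate list, entry threshold or limit on the number of covariates.

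The Random allocation section assigns five centres to the sequential strategy and four to the global strategy.

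Under Assessment of results, the associated-factors item lists what is recorded at centre level: a readiness questionnaire with six dimensions, a leadership scale, and "number of registered patients, number of healthcare professionals, mean number of registered patients per family doctor, and a socioeconomic deprivation index". The staff surveys that supply the centre and professional variables are taken before the strategy, straight after it, and 12 months after the programmes start.

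Table 2 gives the timing of the coverage and execution indicators as "Baseline and 12 months after the setting up of the programme", so each centre's pre-programme rate is available. It is not named as a covariate.

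**The concern.** Arms differ between centres, so the arm effect rests on nine units and 7 degrees of freedom. Randomisation has already removed systematic confounding by baseline factors. Choosing covariates by their relation to the outcome therefore removes no systematic bias, and it lets the arm estimate move with noise. With nine units, a few unrelated centre-level variables can by chance explain much of the between-centre variation. The residual variance then looks too small, and the p-value and interval are computed as if the model had been fixed from the start.

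The article stresses magnitude over significance, which does not remove the problem. The selected model also supplies the point estimate and its 95% interval.

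This is a rule that the article states, not a detail left to a later plan.

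**Working it through.** **Inputs.** From the Sample size section: "an alpha level of 0.05, and an intra-class correlation coefficient (ICC) at centre level of 0.03"; "65% in the sequential group vs 50% in the global group"; "to achieve a statistical power of 80%, allowing for a possible loss of 20% of patients"; "we will need a minimum of 425 patients at high risk of developing T2D" per group. From Random allocation: 5 and 4 centres. From Analysis: over 20,000 patients for the implementation outcomes, about 2,222 per centre. Assumed because the article does not give them: two-sided testing, candidate numbers, selection thresholds, and the correlation r between a centre's baseline and follow-up rates.

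**1. The plan's own figure.** For 65% against 50%, n = [1.96·√(2·0.575·0.425) + 0.84·√(0.2275 + 0.25)]² / 0.15² ≈ 169.3, so 170 per group. With 170/5 = 34 per centre, the design effect is 1 + 33·0.03 = 1.99. Then 170·1.99/0.8 ≈ 423, against 425 stated. After 20% loss, 425·0.8 = 340 per group are evaluable.

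**2. Degrees of freedom.** 9 centres − 2 arms = 7, and each centre-level covariate takes one. The associated-factors item gives about six centre-level scores (four characteristics, readiness, leadership), or 11 if the six readiness dimensions are counted separately (4 + 6 + 1).

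**3. Type I error under the null.** Centre-level simulation: 5 against 4 centres, no arm effect, candidates that are pure noise, arm effect tested with a t reference on the residual degrees of freedom at nominal 5%.

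| Selection | Candidates | Type I error |
|---|---|---|
| None, baseline rate fixed | – | 4.7–5.4% |
| Forward, arm kept | 1–2 centre-level | about 6–8% |
| Forward p<0.10, arm kept | 4 centre-level | about 9–11% |
| Forward p<0.10, arm kept | 6 centre-level | about 14–15% |
| Forward p<0.10, arm kept | 8 centre-level | about 19–20% |
| Backward, arm kept | 7 centre-level | 15–21% |
| Forward, selection ignores arm | several centre-level | about 5% |
| Patient-level factors only, p<0.10 | 7 | 5.0–5.3% |

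Ranges cover separate runs and settings. Results are nearly the same with 94 or 2,222 patients per centre, so the large patient sample does not cure the inflation. With a normal reference, the rate is already about 9% with no selection. That part comes from having few clusters and is not counted here.

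**4. Baseline as a fixed covariate against a pre-post difference.** With k centres of m patients per arm (m = 340/5 = 68 and 340/4 = 85):

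SE² = Σ p(1−p)·[0.03·f + 0.97/m]/k

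Here f = 1 without baseline, f = 1 − r² with a baseline covariate (6 df), and f = 2(1 − r) for a pre-post difference (7 df). Baseline is treated as free of sampling error. Power is from the noncentral t with noncentrality 0.15/SE.

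Without baseline: SE² = 0.2275·(0.03 + 0.97/68)/5 + 0.25·(0.03 + 0.97/85)/4 = 0.00460, SE = 0.0678, noncentrality 2.21, power 48%. This is below the stated 80% because it uses the actual centre sizes and 7 df; that is a separate matter.

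| r | Covariate: SE, power | Pre-post: SE, power |
|---|---|---|
| 0.5 | 0.0616, 53% | 0.0678, 48% |
| 0.7 | 0.0549, 63% | 0.0575, 61% |
| 0.8 | 0.0503, 70% | 0.0516, 70% |

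If the baseline rate is itself estimated from about 76 patients per centre, power falls to 51%, 57% and 61% for the covariate and to 38%, 46% and 52% for the difference.

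**The case against.** The strongest objection is that the inflation depends on conditions the article does not state. The Analysis section speaks only of possible confounders. The one explicit description of adjusters, given for the secondary outcomes, names baseline demographic and clinical characteristics, which are patient-level. The centre-level measures are introduced as associated or modifying factors, which serve the third objective. Nothing says that they enter the stepwise pool, or that values measured after the strategy would be used as adjusters. All of this stands, and it makes the size conditional. It does not remove the point, because the stated rule excludes neither case.

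A second objection is that baseline is already used. This also stands: pre-post differences are planned, and without selection they hold the type I error at about 5%. A reader might infer that the plan discards its main source of precision. The documents do not support that, since at correlations of 0.7–0.8 and with an error-free baseline the planned difference gives nearly the same power as a fixed covariate.

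A third objection is that the article plays down significance. It still reports 95% intervals and sizes the trial at alpha 0.05, and selection alters the estimate itself.

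**Conclusion.** The point holds in conditional form. The article fixes a data-driven choice of covariates for a randomised comparison with 7 centre-level degrees of freedom, and does not restrict the candidates. If 4 to 8 centre-level factors are eligible and the arm term is in the model during selection, type I error is about 10–20% at nominal 5%, and the intervals take no account of the selection. With one or two such candidates it is about 6–8%. With patient-level candidates only, or selection that ignores the arm, it stays near 5%.

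A reader might infer that the trial's false-positive rate is simply doubled to quadrupled. That cannot be stated as fact, because neither the candidates nor the threshold are given. The figures come from a linear model on centre rates with noise covariates, which stands in for the planned multilevel logistic model.

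The gain from a fixed baseline covariate is modest: about 5 percentage points of power over the pre-post difference at an assumed correlation of 0.5, and little at 0.7–0.8. The case for it is mainly that it needs no selection.

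**What to change.** In the Analysis section, replace the stepwise wording for both the main models and the 24-month models with a pre-specified covariate set: the centre's pre-programme value of the same indicator, plus patient age and sex. State that the other centre-level and professional factors are used only in the exploratory associated-factors objective, at values measured before the strategy begins.

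This is a change of wording. The baseline indicators, age and sex are already to be extracted from the health record. The cost is one centre-level degree of freedom (7 to 6), and the main model will not adjust for other chance imbalances between the centres. Those can be shown in a sensitivity analysis labelled as exploratory.

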### Random allocation

The implementation strategy to facilitate the adoption of the recommended clinical intervention for T2D prevention will be common to the two comparison groups (see the following section). In order to distinguish and isolate any effects of the strategy used for the creation of the multidisciplinary community of practice, the centres will be randomly allocated to one of the comparison groups: five centres to the sequential strategy and the other four to the global strategy. This random allocation will be carried out by the members of our research unit not involved in this project, using a computer-generated random number sequence obtained before starting the trial. Given that the new programme is an optimisation of T2D prevention activities already offered by the Basque Health Service, it is expected that participating patients will be blinded to group allocation.

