Regarding the secondary outcome variables, the percentages (e.g. % of patients who meet recommendations on physical activity) were compared using chi-square or non-parametric tests. Quantitative variables were compared using t-tests (comparison of the means). For these outcome measures, pre-post differences and differences between study groups will be estimated, and 95% confidence intervals (CIs) will be calculated on an intention-to-treat basis. Stratified analysis will be performed, mixed-effects generalised models will be built to estimate the differences between the groups adjusted for factors that confound or moderate the effect of the intervention (baseline demographic and clinical characteristics) and adjusted differences, adjusted odds ratios (ORs) and 95% CIs will be calculated at the patient level, taking into account the hierarchical and multicentre structure of data. To explore a potential modifying effect of the intervention on clinical outcomes obtained attributable to the procedure for creating the interprofessional community of practice, we will conduct comparisons by intervention protocol between groups using matching by propensity scores calculated on the basis of the characteristics of patients recorded in their health record. This will permit us to analyse the association between the actual intervention dose received (assessment of lifestyle habits, assessment of habits plus advice, and assessment of habits plus advice plus prescription) and the event of interest (change in lifestyle habits or weight loss) as a function of one or other engagement procedure, pairing patients participating in one or another comparison group in a 1:1 ratio on the basis of them having a similar probability of having received said treatment or intervention dose.

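### The analysis section judges significance by over 20,000 patients, but the sequential-versus-global contrast rests on nine centres, and no between-centre degrees of freedom are named for the models

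*Protocol article*

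**What the plan says.** The Random allocation section assigns whole centres: "five centres to the sequential strategy and the other four to the global strategy". The Sample size section recognises clustering: "Considering the participation of 9 centres, an alpha level of 0.05, and an intra-class correlation coefficient (ICC) at centre level of 0.03". Its target difference is "65% in the sequential group vs 50% in the global group".

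The Analysis section uses multilevel logistic regression for the dichotomous implementation outcomes, with 95% confidence intervals for differences between groups. It then says "As the sample size for evaluating the implementation objectives is over 20,000 patients" and concludes that all comparisons will be statistically significant, so weight will go to the size of the differences in Cohen's categories.

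For the 24-month follow-up, "mixed-effect generalised longitudinal models will be built with fixed effects (intervention group, effect of time on monthly process indicators and interaction time-intervention"), with random intercepts and slopes for subject and doctor-centre. For the secondary outcomes, "mixed-effects generalised models will be built to estimate the differences between the groups", with adjusted odds ratios and 95% intervals that allow for the multicentre structure. SAS is named. The article names no reference distribution, no choice between ML and REML, and no degrees-of-freedom method.

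**The concern.** The claim about significance treats patients as the unit of information. For the comparison of strategies the unit is the centre, and there are nine. The claim therefore sits badly with the sample-size section of the same article, which allows for an ICC of 0.03.

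The same gap bears on the models. Correct random effects put the right variance components into the standard error, but the centre variance is still estimated from nine centres. That uncertainty has to enter through the reference distribution (about 7 df) and a variance estimate that is not biased downwards. This is a different matter from omitting a random effect: it remains when the random-effects structure is right.

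At stake are the between-strategy intervals. A Cohen category reported beside an interval that is too narrow overstates how surely one engagement strategy beats the other.

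**Working it through.** **Inputs.** Centres 5 and 4 (Random allocation). Alpha 0.05, "an intra-class correlation coefficient (ICC) at centre level of 0.03" and a planned difference of 65% - 50% = 15 points (Sample size). Over 20,000 patients (Analysis). Assumptions: 20,000 patients spread evenly over nine centres, rates near 50%, two-sided testing, and a simple comparison of proportions at one time point.

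**1. The plan's claim, taken as if patients were independent.** Patients per centre: m = 20,000/9 = 2,222. Arms: 11,111 and 8,889. SE = sqrt(0.25/11,111 + 0.25/8,889) = 0.00712. Significance threshold: 1.96 x 0.00712 = 1.4 points. On this reading almost any difference would be significant, which is how the claim becomes plausible.

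**2. The same data with the plan's ICC.**
- Design effect = 1 + (2,222 - 1) x 0.03 = 67.6.
- Effective sample = 20,000/67.6 = about 296. The ceiling for nine centres is 9/0.03 = 300, so further patients add almost nothing.
- SE = 0.00712 x sqrt(67.6) = 0.0585.
- Threshold with a normal reference: 1.96 x 0.0585 = 11.5 points.
- Threshold with t on 7 df: 2.365 x 0.0585 = 13.8 points.

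The threshold is thus close to the 15 points the trial is planned to detect. Sensitivity to the ICC: at 0.01 the design effect is 23.2, SE = 0.00712 x sqrt(23.2) = 0.0343, and the thresholds are 6.7 and 8.1 points. At 0.05 the design effect is 112.1, SE = 0.0753, and the thresholds are 14.8 and 17.8 points. Nowhere in this range is significance automatic.

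**3. Type I error if a normal or large-df reference is used.** Degrees of freedom = 9 - 2 = 7.
- Unbiased (REML-type) centre variance: P(|t7| > 1.96) = 9.1%, so a 95% interval covers 90.9%.
- ML centre variance, too small by about 7/9: P(|t7| > 1.96 x sqrt(7/9)) = P(|t7| > 1.729) = 12.8%, so a 95% interval covers 87.2%.

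**4. Simulation check, no true difference, random effects correctly specified.**
- Random-intercept logistic model, ML with Wald z, 1,500 runs per setting, 68 to 2,222 patients per centre, ICC 0.01 to 0.05: rejection 11.3-12.5%. More patients did not lower it.
- Longitudinal model over 25 monthly values with centre random intercept and slope, Wald z, 400 runs each: REML 10.5% (group) and 10.8% (group by time); ML 14.5% and 14.0%. Monte Carlo standard error is about 1.5-1.8 points. This used a linear approximation with assumed variances, and many fits gave convergence warnings, so it supports the closed form and no more.
- A centre-level t-test on 7 df rejected 4.2-5.7%. A 7-df reference placed on ML standard errors still rejected 6-8%, so both the df and the variance estimate matter.

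**5. Price of the correction.** 2.365/1.96 = 1.21, so intervals are 21% wider. Against ML-Wald intervals: 1.21 x sqrt(9/7) = 1.37, so 37% wider.

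**The case against.** The strongest reply is that the article is silent on the reference distribution, and silence is not a choice. A degrees-of-freedom method is a detail that an article commonly leaves to a fuller document, and SAS can be coded to give about 7 df within everything the text says. The models are also described as respecting the grouping by health centre. This stands: a reader might infer that the plan has chosen a normal reference, or has ruled out small-sample inference, and the documents support neither.

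A second reply is that the plan sets significance aside for the implementation outcomes and grades effects by Cohen's categories. This stands as well. A reader might infer that equal strategies will be declared different in about one analysis in ten, but the text gives no p-value rule by which they would be declared so. What survives is the interval: the article promises 95% intervals for between-group differences, and their coverage depends on the reference distribution.

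A third reply is that the 20,000-patient sentence follows the multilevel logistic regression and does not speak of the 24-month or secondary models. That is correct, so the sentence does not prove how those models will be fitted. It is nevertheless a positive statement about the implementation comparisons, and a df option chosen elsewhere would not make it true. It also covers within-centre pre-post contrasts, where patient numbers count for more; the objection here is to the between-strategy comparisons.

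Finally, adjustment for each centre's baseline could reduce the between-centre variance and so lower the thresholds in step 2. It would not add centres or degrees of freedom.

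**Conclusion.** The concern holds in two parts of unequal firmness.

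Firm: the statement that patient numbers make all comparisons significant is wrong for sequential versus global. On the plan's ICC of 0.03 and nine centres, 20,000 patients are worth about 296, and significance needs a difference of about 11.5 points (z) or 13.8 points (t, 7 df). This rests on equal centre sizes, rates near 50% and an unadjusted comparison.

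Conditional: no df or small-sample method is named. If a normal or large-df reference is used, type I error is about 9-13% and 95% intervals cover about 87-91%, even with correct random effects. If about 7 df and a REML-type variance are used, there is no defect in the models.

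Severity is below must-fix. The false sentence needs correcting; the df choice needs stating, but nothing shows that it has been made wrongly.

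**What to change.** 1. Delete or correct the sentence on significance. It should say that the precision of between-strategy comparisons is governed by nine centres.
2. State that every sequential-versus-global effect (12-month, 24-month level, 24-month slope, secondary mixed models) is estimated with a REML-type centre variance and tested on about 7 between-centre df, by Kenward-Roger or between-within. A t-test on centre-level estimates is an acceptable alternative; it agrees only approximately with the mixed model when centre sizes differ.
3. Add, as a sensitivity check, the exact permutation test over the 126 possible 5:4 allocations (9 choose 4 = 126).

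The cost is analysis wording, model options and a short permutation program, with no further data. Intervals become about 21% wider than with a normal reference on the same variance, and up to 37% wider than ML-Wald intervals. That width is the precision that nine centres give.

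### For the secondary outcomes the plan names tests that ignore centres beside mixed models that allow for them, and does not say which carries between-arm inference; the former have about 24–26% false positives at the plan's ICC

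*Protocol article*

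**What the plan says.** The article's Random allocation section assigns nine centres, five to the sequential and four to the global strategy. For the secondary outcomes (physical activity, diet, weight and other risk factors), the Analysis section states two approaches in one paragraph.

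- Simple tests: percentages "were compared using chi-square or non-parametric tests. Quantitative variables were compared using t-tests (comparison of the means". No term for centre, centre-level summary or design-effect correction is attached.
- Models: "mixed-effects generalised models will be built to estimate the differences between the groups", adjusted for confounding or moderating factors. The resulting adjusted differences, odds ratios and confidence intervals are to be obtained "taking into account the hierarchical and multicentre structure of data".

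Between these two statements the paragraph says that both pre-post and between-group differences will be estimated for these outcomes. No sentence says which approach carries the comparison of strategies.

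The Sample size section sizes the weight-loss comparison for a test of equal proportions "using a bilateral chi-squared test for two independent samples with a level of significance of 5" per cent. The same sentence assumes an ICC of 0.03 and 10% loss.

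**The concern.** When centres are randomised, patients of one centre share whatever is peculiar to that centre. A patient-level chi-square or t-test counts each patient as a separate piece of evidence, so its standard error for the difference between arms is too small. The plan accepts that this correlation exists, since it assumes 0.03 for the weight-loss outcome. Enlarging the sample for clustering protects power; it does not repair the false-positive rate of a test that ignores clustering.

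The text does not label the simple tests as between-arm, but that is the natural reading. The second specific objective compares these outcomes between the sequential and global programmes, the sentence after the tests mentions differences between study groups, and the sample-size statement refers to two independent samples. By contrast, the implementation outcomes get multi-level regression from the outset.

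At stake is a reported difference in weight loss or physical activity between strategies that reflects only variation between centres. A naive p-value below 0.05 and a mixed-model interval that includes no difference could both be reported under the present text.

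**Working it through.** **Inputs.** Nine centres, 5 and 4 (Random allocation). ICC 0.03, 616 patients, 10% loss, two-sided 5% (Sample size). Mean patients per centre: 616/9 = 68.4 before loss; 616 × 0.9 = 554, and 554/9 = 61.6 after loss.

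**The plan's own figure.** The Sample size section says "we need 616 patients (308 per group) to achieve a power of 80" per cent, "considering that 10% of patients will attain such change in one of the groups and 35% in the other". A two-sided comparison of 10% with 35% at 80% power needs 43 per group without clustering. With the design effect for 61.6 per centre (2.82, derived below) and 10% loss, this becomes 43 × 2.82 / 0.9 = 135 per group; with 68.4 per centre it is 43 × 3.02 / 0.9 = 144. The nearest variant uses the 175 attending patients per centre: design effect 1 + 174 × 0.03 = 6.22, and 43 × 6.22 / 0.9 = 297. The stated 308 is therefore not reproduced. That is a separate matter: the false-positive rate depends on how many patients per centre are analysed, not on how 616 was reached. I take 616 as stated.

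**Design effect.** DE = 1 + (m − 1) × ICC.

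- m = 61.6: 1 + 60.6 × 0.03 = 2.82; √2.82 = 1.68.
- m = 68.4: 1 + 67.4 × 0.03 = 3.02; √3.02 = 1.74.

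The naive standard error is too small by these factors.

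**False-positive rate of a test that ignores centres.** 2 × (1 − Φ(1.96/√DE)).

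- m = 61.6: 1.96/1.68 = 1.17, giving 24.3%.
- m = 68.4: 1.96/1.74 = 1.13, giving 26.0%.

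Equivalently, a nominal 95% interval at m = 61.6 covers about 100 − 24.3 = 75.7% of the time.

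**Check by simulation** (no true difference, 5 against 4 centres, ICC 0.03). For chi-square there were 40,000 runs per setting, with underlying rates of 10%, 22.5%, 35% and 50%. It rejected in about 24–25% of trials with about 554 patients and about 26–27% with 616. The t-test (20,000 runs) rejected in 24.7% at 62 per centre and 26.0% at 68. On the same binary data, a t-test on the nine centre proportions with 9 − 2 = 7 degrees of freedom rejected in 4.6–5.2%.

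**Sensitivity to the ICC, at m = 61.6.** All values except 0.03 are assumptions.

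| ICC | DE | False-positive rate |
|---|---|---|
| 0.005 | 1.30 | 8.6% |
| 0.01 | 1.61 | 12.2% |
| 0.02 | 2.21 | 18.8% |
| 0.03 | 2.82 | 24.3% |
| 0.05 | 4.03 | 32.9% |

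**The case against.** The strongest reply is that the same paragraph already plans a valid analysis: mixed models for the differences between groups that respect the hierarchical structure. This stands, and it limits the point. A reader might infer that the secondary analysis as a whole runs at about 25% false positives. The document does not support that; the figure belongs only to the chi-square and t-tests. The models do not remove the problem, however, because they are described for adjusted estimates only, and nothing confines the simple tests to description.

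Second, the paragraph does not say what the simple tests compare, and naming a two-sample test in a sample-size statement that also applies an ICC is ordinary practice. Both remarks are fair. Between-arm use is an inference, though a well-supported one.

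Third, precedence between unadjusted and adjusted analyses is commonly left to the statistical analysis plan. If silence on precedence were the only issue, this would be no finding. Here the article states a specific method that is invalid for comparing randomised centres.

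Fourth, Table 2 calls these outcomes an observational comparison, the weight-loss comparison is exploratory, and no success rule rests on it. This lowers the stakes but does not make patients of one centre independent.

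A reader might also infer that the tests are wrong for pre-post change because they are unpaired. The Analysis section does not say whether they are paired, and the independent-samples wording appears only in the sample-size statement about two groups. That inference is unsupported and forms no part of this point.

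**Conclusion.** The concern holds in limited form. The plan names, for outcomes compared between randomised centres, tests that ignore centres, next to models that do not, and leaves open which supports a between-arm conclusion. If the simple tests are used between arms, about one true-null comparison in four would be declared significant at the 5% level.

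This rests on the plan's ICC of 0.03 applying to the outcome in question, on 616 patients spread over nine centres with roughly 62–68 analysed per centre, and on the between-arm reading of the tests. The size depends on the ICC, but the rate stays above 5% at every value examined. The main implementation outcomes are not affected, since multi-level regression is specified for them. The wording should be corrected; the trial's principal conclusions do not depend on it.

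**What to change.** State in the Analysis section that all between-arm inference on the secondary outcomes, unadjusted and adjusted, uses the planned mixed model with a random effect for centre and a small-sample correction suited to nine clusters, or else an analysis of centre-level summaries. State also that chi-square, non-parametric and t-tests applied to individual patients are not used for between-arm p-values or confidence intervals. The sample-size sentence on weight loss should name the same cluster-aware comparison.

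No new data are needed, and the models are already planned. The downside is wider intervals: at ICC 0.03 and 62 patients per centre the standard error rises by a factor of about 1.68 over the naive one, before any small-sample correction. That extra width reflects the information that nine centres actually provide.
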